## **9.2 Cognitive Testing**

Participants will be asked to perform various tasks to assess cognitive function. They will be presented with images, words, numbers, and/or sounds on an iPad.

The NIH Toolbox Cognition Battery (NIHTB-CB) and Cognition Supplemental Measures will be administered by a trained study investigator. The battery has been normed and validated across the lifespan in participants ages 3-85 and its use ensures that assessment methods and results can be used for comparisons across existing and future studies [94, 95]. The constructs and cognitive subdomains to be tested include executive function, working memory, episodic memory, language, processing speed, attention, and learning. In addition to individual measure scores, the battery will yield the following summary scores: Cognitive Function Composite Score, Fluid Cognition Composite Score, and Crystallized Cognition Composite Score [96]. The NIHTB-CB was designed to not exceed 30 minutes in duration. From experience, we anticipate the entire cognitive testing session will last approximately 45 minutes in duration, including setup, the battery, and supplemental measures. Three test versions will be used to reduce practice effects [97].

## **9.3 Muscle Strength Testing**

Previous research in older, untrained women suggests that at least one familiarization session is ideal before strength testing is performed [98]. Therefore, one familiarization session will be performed approximately one week prior to strength testing. The purpose of the familiarization training is to increase the reliability of strength measurements during the testing sessions across participants of various training statuses. Participants will be instructed in proper technique, breathing and full range of motion on all resistance exercises that will be used during testing. The exercises performed will include the leg press, leg extension, leg curl, chest press, lat pulldown, seated row and smith machine seated shoulder press. For muscle strength testing, the 7 exercises practiced during the familiarization sessions will be assessed at baseline, pre-intervention, and post-intervention using 4-6 repetition maximum (RM) strength tests. Participants will complete a warm-up of 5-10 repetitions at an approximate 20RM load, which is estimated based on researcher experience and verbal questions pertaining to training history. One additional warmup set may be used if necessary. Participants will rest for one minute before the first RM attempt. Three attempts will be allowed to reach the final 4-6RM load with a 2-minute rest period between attempts.

The load and number of completed repetitions will be used to estimate 1RM according to the equation [99]: Predicted 1RM (lbs) = (weight lifted in lbs)/(1.0278 – (.0278 x reps))

This equation was chosen based on strong correlations between actual and predicted 1RM values in older adults [100]. The 1RM represents a valid assessment of muscle strength in training-specific exercises in young and older adults [101].

## **9.4 Physical Function Testing**

Physical function tests include the Gait Speed Test [102], Margaria Stair Climb [103], Timed Up-and-Go [104], and Y Balance test [105], which will be assessed at baseline and in the post-intervention period.

Gait Speed Test: Gait speed is an important marker of vitality that can predict the life expectancy of older adults [102]. Tests of gait speed have high validity and reliability in both healthy older adults and patients with dementia [106-108]. Participants will be instructed to walk on a marked 8-meter walkway at a normal, comfortable speed. An examiner will walk behind and to the side of the participant to ensure safety without influencing their gait speed. Time taken to walk the central 4 meters of the course (marked by tape) will be recorded to the nearest hundredth of a second to calculate gait speed in meters/second. An average gait speed of 2 trials will be calculated.

Margaria Stair Climb: Functional power will be measured using a stair climb test that has been successfully performed and correlated with lower-extremity power and mobility performance in older adults with a reliability coefficient of 0.99 [109]. Participants will be instructed to ascend a flight of 10 stairs one step at a time as quickly as possible without using a handrail. Timing will begin when one foot steps on the 3rd stair, and ends when one foot reaches the 9th stair. Time is recorded to the nearest .01 second, and an average of 3 trials is calculated. One practice trial will be given before the 3 trials.

Timed Up-and-Go Test: Mobility will be assessed using the Timed Up and Go (TUG) test, which has been shown to predict immediate fall risk better than static balance tests or isometric muscle strength [110]. A reliability coefficient of 0.98 has been reported [111]. Participants begin seated in a chair with hands on the armrests, are asked to rise, walk to a line on the floor 3 m from the chair, turn around, and return to the same seated position as quickly and safe as possible. Scores will be taken as the time to complete the task, with one practice trial given. An average of time for 3 trials will be calculated.

Y Balance Test: Participants will perform the Y balance test (Functional Movement Systems, Danville, VA), a dynamic balance assessment with validity for predicting risk of lower extremity injury, identifying balance deficits, and responding to training programs [112]. Participants will stand on one foot on a stance platform from which 3 pieces of polyvinylcholoride pipe, marked in 5 mm increments, extend in the anterior, posteromedial, and posterolateral directions. The participant will be instructed to push a target with the foot of the reaching limb in each of the 3 directions. Maximal reach is recorded for each foot, in each of the 3 directions. A practice trial is given for each foot in each direction.

## **9.6 Body Composition**

Lean body mass (LBM), fat mass (FM), percent body fat (PBF), bone mineral content (BMC), and bone mineral density (BMD) will be measured by dual energy x-ray absorptiometry (DXA). Patients will be positioned supine on the scanner for approximately 12 minutes to complete a whole body, spine, and hip scan. We will also measure total body fat using the InBody 770 (Biospace, Inc) bioelectrical impedance device to compare bioelectrical impedance measures of body fat to DXA measures of body fat in this population. The patients will stand on a scale-like device for approximately 30 seconds while a non-detectable electrical current is passed through their body from the hand and foot contacts to determine impedance from which body fat is calculated.

## **9.7 Blood Pressure**

Blood pressure will be assessed using a sphygmomanometer at the brachial artery while the patient is seated.

## **9.8 Estimated VO2max Testing**

Participants will complete a submaximal treadmill exercise protocol to estimate maximal oxygen consumption (VO2max), a measure of aerobic capacity. The single-stage submaximal treadmill walking test was validated by correlating the estimated VO2max to the measured VO2max (R^2^ = 0.92) [113]. A polar heart rate monitor will be used to measure heart rate during the test. Participants will warm-up for 4 minutes at a 0% grade and a walking speed (recommended speed: 3.4-4 mph) that brings their heart rate to 50%-70% of her/his age-predicted max heart rate (220-age). After the warmup, the treadmill grade will be increased to 5%, and the participant will continue to walk at the same speed for an additional 4 minutes. Steady-state (SS) heart rate will be recorded. The formula for estimated VO2max is:

Estimated VO2max (ml·kg^-1^·min^-1^) = 15.1 + 21.8 (speed in mph) – 0.327 (SS heart rate in bpm) – 0.263 (speed x age) + 0.00504 (SS heart rate x age) + 5.98 (gender; female = 0, male = 1).

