## **2.3 Exploratory Objectives**

1. To determine whether changes in cerebrovascular function mediate the relationship between RT and improvements in cognition.

2. To evaluate intervention effectiveness and explore potential mechanisms of benefit using various physical, physiological, and biochemical outcomes. These outcome measures include: 1) physical capacity (muscle strength and maximal oxygen consumption), body composition, and functional mobility; 2) putative blood markers of exercise-induced brain plasticity (i.e. BDNF, IGF-1, and VEGF); 3) cardiovascular risk factors (i.e. blood pressure) and markers of endothelial dysfunction (i.e. tissue plasminogen activator (t-PA) and Von Willebrand factor (VWF)); and 4) brain morphology (e.g. volume, cortical thickness, and white matter lesions) and resting state brain activity.

3. To investigate associations between brain adaptations and potential mechanisms of benefit. Changes in the above outcome measures will be examined for their roles in mediating RT-induced changes in cognition and cerebrovascular function.

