## **5.1 Inclusion Criteria**

The patient must give written informed consent to enter into the study after receiving a full explanation of the study's purpose, procedures, and risks. A copy of the consent form for this protocol will be given to each subject entering the study. All of the following criteria must be met for the subject to be eligible for the study:

- 60-80 year old men and women.
- Community-dwelling and living independently (without need of assistance).
- Interest and availability for participation in a 12-week planned RT program at the CERC, including pre- and post- testing.
- Competency in English sufficient for assessment and training.
- Able to see and hear sufficiently to participate in RT.
- Not engaged in any structured exercise training outside of this intervention.
- Eligible to undergo MRI.
- Answer NO to all questions on the Physical Activity Readiness Questionnaire (PAR-Q) or receive medical clearance from a physician.

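### At a fixed walking speed, the VO2max equation in 9.8 reverses the effect of heart rate above about age 65, so a change in the estimate cannot be read as a change in fitness

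*Protocol*

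**What the plan says.** Section 9.8 describes a single-stage submaximal treadmill walk and prints the equation used to score it. The intercept and speed term are "15.1 + 21.8 (speed in mph" and the sex term is "5.98 (gender; female = 0, male = 1". Between them stand the terms that matter here, "0.327 (SS heart rate in bpm) – 0.263 (speed x age) + 0.00504 (SS heart rate x age", the first of which carries a minus sign.

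The warm-up is walked on the flat at a speed described as "recommended speed: 3.4-4 mph) that brings their heart rate to 50%-70% of her/his age-predicted max heart rate (220-age". The grade is then raised to 5% and "the participant will continue to walk at the same speed for an additional 4 minutes"; the steady-state heart rate is recorded. Speed is thus held within a test. The section does not say whether it is held from one visit to the next. It cites a validation R² of 0.92 and gives no age range for that validation.

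Section 5.1 enrols "60-80 year old men and women". Section 2.3 lists among the outcomes of exploratory objective 2 "physical capacity (muscle strength and maximal oxygen consumption), body composition, and functional mobility", and under objective 3 changes in these outcomes are examined as possible mediators. Sections 3.0 and 9.10 schedule the test at baseline, pre-intervention and post-intervention. Section 13.1 applies the mixed model to the objective 2 outcomes and Spearman correlations of change to objective 3.

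**The concern.** A submaximal test of this kind rests on one idea: at the same external workload, a fitter person has a lower heart rate. The estimate should therefore rise when heart rate falls. In the printed equation heart rate also enters through a positive product with age, which works against the negative main effect. If that product outweighs the main effect within the eligible ages, the score runs the wrong way for part of the sample.

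The estimate feeds a period comparison and a set of rank correlations of change. If the same fall in heart rate counts as improvement at one age and deterioration at another, the ranks no longer order participants by change in fitness. An apparently null VO2max result would be hard to interpret too. The background in section 1.2 says that cognitive gains from resistance training are not associated with aerobic capacity, and a score that hardly responds to heart rate could seem to bear that out.

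**Working it through.** **Inputs.** From 9.8: speed +21.8 per mph; heart rate −0.327 per bpm; speed × age −0.263; heart rate × age +0.00504; intercept 15.1; men +5.98. From 5.1: ages 60 to 80. The protocol gives no worked VO2max value to reproduce.

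**Heart-rate slope at fixed speed.** Differentiating the equation by heart rate gives −0.327 + 0.00504 × age. Sex and speed drop out. The slope is zero at 0.327 / 0.00504 = 64.88 years. Allowing for rounding of the printed coefficients, the crossing lies between 0.3265 / 0.005045 = 64.7 and 0.3275 / 0.005035 = 65.0 years.

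**Share of the eligible range.** (80 − 64.88) / 20 = 15.12 / 20 = 75.6%.

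**Speed slope.** Differentiating by speed gives 21.8 − 0.263 × age, which stays positive up to 21.8 / 0.263 = 82.9 years, beyond the eligible range.

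**Sizes.** The 10 bpm fall and the 0.2 mph increase are illustrations of mine, not protocol figures. Changes in score are in ml/kg/min.

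| Age | Heart-rate slope per bpm | Change for −10 bpm | Speed slope per mph | Change for +0.2 mph |
|---|---|---|---|---|
| 60 | −0.0246 | +0.25 | 6.02 | +1.20 |
| 65 | +0.0006 | −0.01 | 4.71 | +0.94 |
| 70 | +0.0258 | −0.26 | 3.39 | +0.68 |
| 75 | +0.0510 | −0.51 | 2.08 | +0.42 |
| 80 | +0.0762 | −0.76 | 0.76 | +0.15 |

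**Full equation, one case.** Take a woman of 75 walking at 3.4 mph. Her age-predicted maximum is 220 − 75 = 145, so 50% and 70% of it are 72.5 and 101.5 bpm. I use these as example steady-state values, although the protocol applies the window to the warm-up.

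- At 72.5 bpm: 15.1 + 74.12 − 23.71 − 67.07 + 27.41 = 25.85.
- At 101.5 bpm: 15.1 + 74.12 − 33.19 − 67.07 + 38.37 = 27.33.

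The higher heart rate at the same speed scores about 1.5 ml/kg/min better (29 × 0.051 = 1.48).

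**Speed against heart rate.** The rise in score from 0.1 mph more speed offsets a heart-rate fall of 0.339 / 0.0258 = 13 bpm at 70, 0.2075 / 0.051 = 4 bpm at 75 and 0.076 / 0.0762 = 1 bpm at 80. So up to about 70 a change in the score mainly reflects the chosen speed. Towards 80 the speed term fades and the reversed heart-rate term carries more of it.

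**The case against.** The best defence is that the reversal holds only when speed is fixed. Speed is chosen by a heart-rate target, so a participant who becomes fitter may be tested faster, and the positive speed term then raises the score. That is correct, and the estimate is not blind to fitness in every case. It does not rescue the outcome, for two reasons. The target window is wide (29 bpm at age 75), so fitness does not determine which speed is used. And 9.8 does not say whether speed is re-chosen or repeated at later visits. If it is repeated, the heart-rate slope decides the change, with the wrong sign above 64.9. If it is re-chosen, the change depends on that choice, and near 80 even a faster speed adds little.

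The size also deserves a fair description. The slope at 60 (−0.025) and at 70 (+0.026) are about equal in magnitude. Around 60 to 70 the honest summary is that the score barely responds to heart rate; the reversal becomes more marked towards 80.

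A reader might infer several stronger things that the documents do not support:

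- That the sign is wrong in most participants. The protocol gives no expected age distribution; only the share of the eligible range can be derived.
- That the score can never show a gain at fixed speed. Below 64.9 it can, though weakly.
- That every correlation or mediation result using it must be wrong. The speed term may still carry some signal.
- That ageing between visits biases the comparison. Test-to-test intervals in 9.10 are of similar length in the two periods, so age steps add mostly noise and roughly cancel.

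**Conclusion.** The point stands as a statement about the printed equation: at fixed speed the heart-rate effect is weakly negative at 60, vanishes at about 64.9 years and is reversed over 15.1 of the 20 eligible years. No other section corrects this. Because speed is not tied across visits, a change in estimated VO2max mixes speed choice with a weak or reversed heart-rate effect and cannot be interpreted as a change in fitness in the exploratory models or Spearman correlations.

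The consequence is limited. Cerebrovascular function and cognition, the primary and secondary outcomes, do not use the equation. At its largest the reversed effect is 0.76 ml/kg/min per 10 bpm.

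The sign and the crossing age rest only on the printed coefficients; the ml/kg/min sizes rest on the illustrative 10 bpm and 0.2 mph. A reader might conclude that the coefficients were miscopied. The documents cannot show whether that is so or whether a correctly copied equation is being applied outside its valid ages. Either way 9.8 should change.

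**What to change.** 1. Check the coefficients and the valid age range against the cited validation study. If a coefficient was miscopied, correct it and recompute the heart-rate slope at 60, 70 and 80.
2. State in 9.8 that each participant walks at the same speed at all three tests where feasible, and that any departure is recorded.
3. Name the steady-state heart rate at 5% grade, at the repeated speed, as the aerobic-fitness outcome for exploratory objectives 2 and 3.
4. Report an estimated VO2max only from an equation whose heart-rate slope stays negative across 60 to 80 years.

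The cost is wording in 9.8 and in the outcome list. Steady-state heart rate is already recorded and speed is already needed for the equation, so no procedure is added. There are two drawbacks: the outcome is no longer in ml/kg/min and is harder to set beside other studies, and with speed repeated the post-training warm-up heart rate may fall outside the 50–70% window for some participants. The protocol should say how those cases are handled.

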## **9.9 Questionnaires**

The following questionnaires will be administered:

The Physical Activity Readiness Questionnaire (PAR-Q) will be administered for eligibility screening to determine whether potential participants are healthy enough and have sufficient baseline fitness levels for exercise training. If a potential participant answers “yes” to any questions on the PAR-Q, they will be encouraged to check with their doctor before becoming much more physically active, and will be required to receive medical clearance from a physician to participate in this study.

The Mini-Mental State Examination (MMSE) is the most commonly applied test to screen for cognitive deficits [114]. The MMSE will be administered for eligibility screening to determine the mental status of potential participants. The maximum score is 30. A score of 23 or lower is indicative of cognitive impairment, and will preclude the patient from participating in this study. These patients will be referred to a clinician with experience in dementia assessment.

Physical activity levels will be assessed using the International Physical Activity Questionnaire (IPAQ), administered at baseline, pre-intervention, and post-intervention. The IPAQ has been validated in adults over the age of 18 with varying activity levels across 12 countries [115]. The IPAQ aims to identify physical activity and exercise habits, and will be used to determine the average volume of activity over 1 week in metabolic equivalents (METs).

Quality of life (QOL) is an important domain for dementia assessment [1]. Increased physical activity can improve QOL in healthy older adults [116, 117], frail older adults [118], and patients with mild cognitive impairment [119]. To test the effects of the RT intervention on QOL, the Satisfaction With Life Scale (SWLS) will be administered at baseline, pre-intervention, and post-intervention [120]. Research using the SWLS suggests that it is sensitive enough to detect changes in life satisfaction over time [121]. In addition, general health-related quality of life status will be assessed using the Short Form-36 (SF-36) [122].

Sleep is an important consideration for cognitive performance in older adults [123]. Poor sleep is associated with impaired cognitive function [124, 125]. The Pittsburgh Sleep Quality Index (PSQI) will be administered at baseline, pre-intervention, and post-intervention to evaluate sleep quality. The clinemetric properties of the PSQI have made it a standard assessment for clinical research in older adults [126-128].

Social interaction and engagement are important confounding variables in intervention studies targeting cognitive health [34, 129]. The Interpersonal Support Evaluation List (ISEL) is a validated measure of perceptions of social support [130] that will help us understand whether the effectiveness of our intervention is modified by perceptions of social support, i.e. to control for the influence of social interaction during personal one-on-one exercise training.

## **9.10 Study Calendar**

|  | Week # | Day 1 | Day 2 | Day 3 |
| --- | --- | --- | --- | --- |
|  | 0 | Informed Consent  Eligibility |  |  |
| Baseline Tests | 1-2 | **Testing Part 1:**  Cognitive Testing  QOL Questionnaires  PSQI  MRI Scan | **Familiarization Day:**  Descriptive Factors  Exercise Familiarization | **Testing Part 2:**  IPAQ  Blood Pressure  Body Composition  Blood Draw  Physical Function  Muscle Strength  Estimated VO2max |
| Control | 3-14 | 12-week Control Period | | |
| Pre Tests | 15 | **Testing Part 1** | **Testing Part 2** |  |
| RT | 16-27 | 12-week RT Intervention | | |
| Buffer Period  (if necessary) | 28-29 | Missed Session Completion | | |
| Post Tests | 28-29, 29-30, or  30-31 | **Testing Part 1** | **Testing Part 2** |  |

# **10.0 Criteria for Evaluation and Endpoint Definitions**

The outcome status of all eligible patients will be reported. Endpoint definitions include completion of the resistance training program with at least 80% of the sessions attended and baseline and post-intervention measurements for all variables.

# **11.0 Special Instructions**

N/A

# **12.0 Data Collection and Monitoring**

All data will be de-identified to prevent participants’ identities from being connected with their information. Each participant will receive a Patient Identification number. Data will be stored in a locked file cabinet in an office (CHP-149). All data will be inputted into a digital spreadsheet for subsequent use/analyses. Only members of the study team will have access to the digital spreadsheets.

# **13.0 Statistical Considerations**

## **13.1 Statistical Analysis Plan**

Participant characteristics will be described at baseline. Continuous variables will be examined for normality and described by either means and standard deviations or medians and interquartile range (if not normal); categorical variables will be described with N (%) of each category. Participant characteristics will be compared with missing data and attrition to determine if there are any systematic patterns that should be adjusted for in secondary analyses; any difference with p < 0.25 will be used in secondary analyses to see if there is an effect on the intent-to-treat model.

Comparison of cerebrovascular function (Hypothesis 1) and cognition (Hypothesis 2) between groups will follow intent-to-treat models using longitudinal linear mixed effects modeling to assess the change in these outcomes, with the main factor of period – control versus RT. The stratifying factor of gender will also be included in the model, as is standard. This same modeling will be used to test whether cerebrovascular function mediates the effect of group assignment on cognition by adding cerebrovascular function to the model of cognition and examining the change in the beta coefficient of group (exploratory objective 1). A change in beta coefficient of >20%, will be considered indicative of mediation. Because these data will be preliminary, the primary endpoint will be the effect size calculated from the estimated marginal means of differences in the change by period from the models. This can then be translated more directly into potential clinical effect.

This same modeling technique will be used for outcomes defined in exploratory objective 2. To assess the association of changes in cerebrovascular function and cognition with other outcomes (exploratory objective 3), Spearman correlations of change in outcomes, adjusted for baseline level will be computed for the total group, and stratified by group assignment.

All analyses will be performed with SPSS (v.24).

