# **3.0 Study Design**

This study will be conducted in the Clinical Exercise Research Center (CERC) in the Division of Biokinesiology and Physical Therapy on the University of Southern California Health Sciences Campus. In this mechanistic proof-of-concept clinical trial, the effects of a 12-week periodized RT intervention on the brain will be compared to that of an initial control period of equal duration. After baseline testing, participants will be asked to resume normal life for the 12-week control period. After the control period, and before the RT intervention, participants will undergo the same tests performed at baseline. Post-intervention, participants will be tested again (please see study calendar 9.10).

**Study Visit 1:** Interested participants will report to the CERC and read the informed consent with a study investigator. The prospective participant will be given the opportunity to ask any questions they may have about the study. If the potential subject is willing to take part in the study, she/he will sign the informed consent agreeing to participate. She/He will also complete a Physical Activity Readiness Questionnaire (PAR-Q) to ensure she/he is at a baseline fitness level necessary for exercise training, and a Mini-Mental State Examination (MMSE) to screen for cognitive deficits. All potential subjects will have their blood pressure taken during this visit to ensure normal levels. Additional screening will take place, according to the inclusion/exclusion criteria.

**Study Visit 2 (Baseline Testing Part 1):** All participants will undergo the following tests: cognitive testing, quality of life questionnaires, and MRI scans. Approximate time: 2.5 hours

**Study Visit 3 (Baseline Familiarization Day):** Descriptive factors will be measured on all participants. Then they will undergo exercise and testing familiarization. Approximate time: 1.5 hours

**Study Visit 4 (Baseline Testing Part 2):** All participants will undergo the following tests: International Physical Activity Questionnaire (IPAQ), blood pressure, body composition, blood draw, Physical Function tests, Muscle Strength tests, and estimated VO2max tests. Approximate time: 2.5 hours

**Control Period:** Participants will be encouraged to continue normal activities of daily living and eating routines.

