## **13.2 Sample Size and Power Considerations**

Because this is a proof-of-concept clinical trial, sample size will be determined based on feasibility and study funding. Previous investigations on CBF after 12 weeks of aerobic exercise [47] suggest that 20 participants per group is sufficient to determine response variance and effect sizes to establish preliminary signals of efficacy. Attrition rate is anticipated to be 15%, a conservative estimate, as the attrition rate of previous RT interventions of similar length (12 weeks, 3days/week) in healthy older adults is about 5.7% [131]. Our previous RT intervention in older adult men, upon which the current study’s RT program is based, had no dropouts due to injury, illness, or personal choice [80]. Accounting for 15% attrition (~3) yields a final, proposed sample size of 23.

Sensitivity analysis using these parameters was performed in G*Power 3.1.9.2. With the proposed sample size of 23, we would have sufficient power to statistically detect a large effect size d between dependent means of 0.611 with α = 0.05 and 1-β = 0.80.

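### The primary model compares two changes that share the week-15 value without fixing a covariance that allows their negative correlation, so its standard error can be too small

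*Protocol*

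**What the plan says.** Section 13.1 of the protocol describes the analysis of both hypotheses as "longitudinal linear mixed effects modeling to assess the change in these outcomes, with the main factor of period – control versus RT". It adds that "the primary endpoint will be the effect size calculated from the estimated marginal means of differences in the change by period". It names no random effect or residual covariance, and it does not say whether the rows of the data set are change scores or visit values.

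Section 3.0 describes the shared test point: "After the control period, and before the RT intervention, participants will undergo the same tests performed at baseline". Sections 9.0 and 9.10 confirm three test points: baseline (weeks 1–2), pre-intervention (week 15) and post-intervention.

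Section 13.2 reports a sensitivity calculation: "With the proposed sample size of 23, we would have sufficient power" to "detect a large effect size d between dependent means of 0.611" "with α = 0.05 and 1-β = 0.80". It does not say which two means are compared or which SD standardises d. On numbers it says "Accounting for 15% attrition (~3) yields a final, proposed sample size of 23".

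**The concern.** Taken literally, section 13.1 gives two rows per participant, the control change and the RT change, and the main effect of period is the difference between them. The week-15 measurement enters the first row with a plus sign and the second with a minus sign. A high week-15 reading caused by error alone makes the control change look large and the RT change look small, so error at that visit pushes the two rows in opposite directions.

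The common default in a mixed model is a random intercept per person. It represents only zero or positive correlation between rows. Faced with a negative one, it sets the intercept variance to zero and treats the rows as independent. The variance of their difference then omits the covariance term that should increase it.

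This study exists to supply effect sizes and response variance for later planning (section 2.1). An interval that is too narrow, or an effect divided by an SD that is too small, would carry over into the design of the next trial. The same modelling is also planned for the outcomes of exploratory objective 2.

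**Working it through.** **1. The plan's own figure.** Inputs from section 13.2: n = 23, α = 0.05, power 0.80. For a two-sided paired t test with 22 degrees of freedom, the noncentral t distribution gives a detectable dz of 0.6113, and power at 0.611 of 0.7996. The stated 0.611 is reproduced. It is mean difference / SD of the paired difference.

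**2. Assumptions.** The protocol gives no SD or correlation. Call the visit values Y1 (baseline), Y2 (week 15) and Y3 (post). Let σ² be an independent error variance at each visit and τ² the between-person variance of a trend common to both periods. The ratio τ²/σ² is varied from 0 to 2.

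**3. Variances.**
- D1 = Y2 − Y1 and D2 = Y3 − Y2 each have variance 2σ² + τ².
- Cov(D1, D2) = τ² − σ², so the correlation is (τ² − σ²)/(2σ² + τ²): −0.5 at τ² = 0, −0.2 at τ² = 0.5σ², 0 at τ² = σ², and +0.25 at τ² = 2σ².
- The primary contrast is D2 − D1 = Y3 − 2·Y2 + Y1. Its variance is (1 + 4 + 1)σ² = 6σ² per person, whatever τ² is.
- If the rows are treated as independent, the variance used is 2(2σ² + τ²) = 4σ² + 2τ².

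At τ² = 0 the standard error ratio is √(4/6) = 0.816. An effect standardised by the SD that this model implies is inflated by √(6/4) = 1.22.

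**4. Type I error.** Simulation at n = 23 with 200,000 trials per row. The random-intercept variance is bounded at zero, with 2n − 2 degrees of freedom when it is at the bound and n − 1 otherwise.

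| τ²/σ² | Mean SE / true SE | Type I error, random intercept on changes | Type I error, paired contrast |
|---|---|---|---|
| 0 | 0.81 | 10.8% | 5.0% |
| 0.25 | 0.86 | 8.9% | 5.0% |
| 0.5 | 0.90 | 7.5% | 5.0% |
| 1 | 0.95 | 5.9% | 5.0% |
| 2 | 0.98 | 5.1% | 5.0% |

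Results at n = 20 are nearly the same (10.7% at τ² = 0, 7.5% at 0.5). Using n − 1 degrees of freedom throughout, the limiting case at n = 23 is 9.9%. Smaller simulation runs gave 7.4% to 7.6% in the third row and 6.0% to 6.4% in the fourth. A check at τ² = 0 with a standard mixed-model routine (100 trials) gave an SE ratio of 0.83 and 10% rejections.

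**5. Random intercept on the three visit values.** With visit as a category, this gives 5.1% at τ² = 0. It becomes conservative as trend variance grows: 3.1% at 0.25 and 0.8% at 1 (n = 23). A plain random intercept is therefore not safe in either layout.

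**6. Expected completers.** At n = 20 the detectable dz is 0.660, and power at 0.611 is 73.6%.

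**The case against.** The strongest reply is that the faulty model is not in the document. Section 13.1 names neither a random intercept nor change-score rows. Calling the model longitudinal leaves room for a fit to the three visit values, with the difference in changes taken from the marginal means. Covariance structure is also commonly left to a separate statistical analysis plan, which may exist and is not shown. This stands. A reader might infer that the planned intervals and p-values are too optimistic, but the protocol does not establish that. An unstructured covariance on the two changes would also avoid the problem. What remains is that the response and the two-level factor, as worded, lead naturally to the layout in which the default fit fails.

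It is also fair that 11% is a limiting case. It needs independent visit errors and no variation in trend between people, and the protocol gives no figures to place the trial within the range.

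Three stronger readings are tempting and do not hold:
- Labelling baseline and week 15 as control and the last visit as RT would credit one and a half intervals of drift to RT. That contrast is not a difference in change, so it conflicts with the stated primary endpoint.
- Power of 32% (n = 20) to 37% (n = 23) follows only if 0.611 is in SDs of a single 12-week change, giving dz = 0.611/√3 = 0.353 at τ² = 0. Section 13.2 does not say so. The two period changes are themselves dependent means, and on that reading 0.611 is on the scale of the primary contrast.
- The protocol does not say that the effect size is unitless. Reporting in native units is a preference.

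**Conclusion.** The concern holds as a conditional risk. The stated layout makes the two modelled changes share a measurement, and nothing in the protocol ensures that the model allows the resulting negative correlation. If a random intercept is fitted to the change scores, type I error lies between about 5% and 11%. It is highest when visit error dominates and close to nominal once trend variance is twice the error variance. The standard error is then between about 0.81 and 0.98 of its true value. These figures assume equal, independent visit errors, a trend common to both periods, and complete data. Under complete data the estimated difference itself does not change.

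The arithmetic behind 0.611 is correct. Its scale is unstated and it uses all 23 enrolled. Both are matters of clarification and do not show the study to be underpowered.

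**What to change.** In section 13.1, state that the model is fitted to the three visit values, with visit as a three-level fixed factor and an unstructured within-person covariance. Make (Post − Pre) − (Pre − Baseline) = Post − 2×Pre + Baseline the primary contrast, reported with a 95% confidence interval. Computing that contrast once per person and analysing it as a paired difference is an acceptable alternative, but it drops anyone who lacks a visit. The three-visit model keeps their partial data, which suits the intent-to-treat aim. Gender can stay in the model.

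In section 13.2, state that "effect size d between dependent means of 0.611" is the paired dz of this contrast at n = 23, standardised by the SD of the difference in changes. Add the figures for the 20 expected completers: detectable dz 0.66, and power of about 74% at 0.611.

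The cost is a few sentences. No new data are needed and the analysis runs in the planned SPSS. The standard error may come out somewhat larger than under a random intercept on change scores.
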